#### Complier average causal effect (CACE) analysis

A blinded review of compliance will be conducted by study investigators and the data management team prior to data analysis to determine whether a CACE analysis is required. If appropriate, CACE analysis will be performed on HbA1c at 12 months (primary outcome) to assess the size of the benefit of the intervention in those who comply with the intervention. Unlike a per-protocol analysis (PP), CACE analysis preserves randomisation when estimating the intervention effect [30]. This is achieved by comparing the mean HbA1c of ‘compliers’ in the intervention group (defined in Table 7) with a similar group of control participants who would have complied if they were offered the intervention. The outcome of the analysis is the CACE effect which represents the difference in mean HbA1c between compliers in the intervention group and their counterpart compliers in the control group.

**Table 7 Tab7:** Definition of a complier for the complier average causal effect (CACE) analysis

The following four requirements must be met for a participant to be considered a complier:	
1. Participant attended the educational session at baseline with the study credentialed diabetes educator (CDE)	
2. General practitioner attended a face-to-face group education session or an education session with the study CDE or completed online training	
3. Participant wore a continuous glucose monitoring (CGM) sensor at baseline, 3 months, 6 months, and 9 months	
4. Participant attended clinic assessment visit (CAV) and discussed sensor trace at baseline, 3 months, 6 months, and 9 months	

The method assumes the same proportion of participants in the control group would have complied with the intervention if it was offered to them as those who did comply in the intervention group (A% in Table 8) [30]. Another important assumption is that mean HbA1c at 12 months is the same for non-compliers in both the intervention and control groups (x in Table 8) [30]. It is this assumption that allows the mean HbA1c of the (expected) compliers in the control group to be calculated (using the observed mean HbA1c in the control group). The CACE effect is then calculated as the difference in mean HbA1c between actual compliers in the intervention group and expected compliers control group. This will be reported with 95% confidence intervals.

**Table 8 Tab8:** Complier average causal effect (CACE) analysis

Status	Intervention group		Control group	
	Proportion (%)	Mean HbA1c	Proportion (%)	Mean HbA1c
Complier	A%	y	A%	z
Non-complier	B%	x	B%	x
Overall		Observed mean HbA1c		Observed mean HbA1c

*HbA1c* glycated haemoglobin

#### Sensitivity analysis

The missing data patterns will be described and the drop-out rates between the two study groups will be compared. A sensitivity analysis will be performed on the primary analysis for HbA1c at 12 months to test the robustness of the missing data assumption using a pattern-mixture model. Under the mixed-effects model, missing data are assumed to be missing at random [28]. Under this assumption, the difference between the mean of the missing data and the mean of the observed data *δ* is assumed to be zero. In a pattern-mixture model, a range of plausible values for *δ* other than 0 will be considered, where positive values of *δ* would indicate that, on average, participants who have missing data have higher (worse) HbA1c than observed participants, and negative values of *δ* assume participants with missing data have lower (better) mean HbA1c than observed participants. Results for plausible values of *δ* will be examined to determine whether study conclusions change for departures from the missing at random assumption in the primary analysis.

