#### Statistical modelling

##### Primary and secondary outcomes

Whilst our primary outcome is HbA1c at 12 months post-intervention, we will estimate the between-group difference in mean HbA1c at 6 and 12 months with the same linear mixed-effects model using restricted maximum likelihood estimation. As the data are longitudinal, HbA1c measured at baseline, 6 months, and 12 months will be included in the model as the dependent variable and study groups (intervention and control) and time of the pathology result (baseline, 6, and 12 months) will be collected as fixed effects. A two-way interaction term between study group and time will be included in the model to estimate the between-group difference in mean HbA1c at 6 and 12 months, but we will constrain the estimated baseline means to be equal. The model will include random intercepts for clinic (as individuals will be clustered within clinics) and individuals (as patient measures are repeated within individuals). An unstructured variance-covariance structure will be assumed for the random effects variables as correlations between measurements within individuals and correlations between measurements in participants from the same clinic are expected to be unique.

Age, index of relative socio-economic disadvantage (IRSD), and a history of severe hypoglycaemia are known to be at least moderately associated with HbA1c [9, 27]. In a secondary analysis, the outcome measure will be adjusted for these potential confounders. These measures will be included as fixed effects in the model.

An intention-to-treat (ITT) approach will be used where participants will be analysed according to the study group they were assigned, and all participants will be included in the analysis, consistent with mixed model analysis [28]. The estimated mean HbA1c levels at baseline, 6 months, and 12 months will be plotted for each study group with 95% confidence intervals.

The same statistical modelling approach described for HbA1c will be used for the secondary outcomes, percentage time in target and diabetes-specific distress at 12 months. Transformations for skewed outcome measures will be considered.

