## Discussion

The design effect is a multiplier applied to sample size calculations for an individually randomised trial to account for the sampling method, such as stratified or cluster randomisation. In this study, participants will be randomly allocated to study groups stratified by the clinic they attend. For stratified randomised trials the design effect is (1 – ICC), where the intraclass correlation coefficient (ICC) quantifies the correlation of outcomes within clinics. Applying this design effect to the sample size calculations will reduce the number of individuals required for the same power as an individually randomised controlled trial with no stratification when the ICC is greater than zero [31]. For this study, we chose the more conservative sample size that did not adjust for stratification by clinic, that is the ICC was assumed to be zero to avoid challenges associated with estimating the ICC.

Randomly permuted block sizes of 4 and 6 were chosen to minimise differences in the number of participants in each study group should recruitment stop abruptly in a clinic and to ensure adequate participants in each study group for estimation of clinic effects. Random effects were chosen to model the clinic effects as we assumed clinics involved were a random sample across Victoria. Furthermore, random-effects models can perform better than fixed-effects models in terms of power and efficiency when there are a small number of participants per clinic and there are treatment assignment imbalances within clinics [32]. Lastly, the mixed-effects model includes all data observed on the subjects and satisfies the intention-to-treat principle in the presence of missing outcome data, provided the missing at random assumption holds.

This analysis plan was written prior to completion of the trial data collection phase. Analyses are pre-specified, consistent with the study objectives, and not driven by the data. An outcomes paper based on this analysis plan will be available upon completion of data collection, which is anticipated in late 2018.

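### The pattern-mixture check equates missing at random with equal means of missing and observed HbA1c, so δ as worded does not measure departure from the primary model's assumption

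*SAP article*

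**What the plan says.** The Sensitivity analysis section of the SAP article starts correctly: "Under the mixed-effects model, missing data are assumed to be missing at random". It then translates that assumption into a value of δ: "Under this assumption, the difference between the mean of the missing data and the mean of the observed data", written δ, is zero. Values other than zero form the pattern-mixture analysis. A positive δ is explained as meaning that, on average, "participants who have missing data have higher (worse) HbA1c than observed participants", and a negative δ as the reverse. The plan will consider "a range of plausible values for" δ, and the stated purpose is "to determine whether study conclusions change for departures from the missing at random assumption in the primary analysis".

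No numerical range is given. There is one symbol with no arm index, and the text does not say whether δ is the same in both arms or may differ. The same section does plan to describe the patterns of missingness and to compare drop-out by arm.

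The assumption being tested belongs to the model in the section Primary and secondary outcomes: "HbA1c measured at baseline, 6 months, and 12 months will be included in the model as the dependent variable". That model has group, time and their interaction as fixed effects, with random intercepts for clinic and participant.

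**The concern.** In a mixed model fitted to repeated HbA1c values, missing at random allows participants without a 12-month value to differ on average from those with one, provided the difference is explained by what was observed: arm, clinic, and baseline and 6-month HbA1c. Equal unconditional means is a condition of the missing-completely-at-random kind. Two things follow. The scale for δ starts from the wrong zero. And a participant group that is worse at 12 months only because it was already worse at 6 months would be counted as a departure from missing at random when it is none.

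A second question is whether δ may differ by arm. A treatment contrast responds to δ mainly through differences between the arms, so the answer decides whether the check can inform at all.

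This is the only sensitivity analysis the article describes for missing primary-outcome data. The sample size allows for 20% participant attrition, and the Discussion rests the intention-to-treat property of the mixed model on the same assumption.

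**Working it through.** **Inputs from the document (Sample size section).** SD 1.3 and target difference 0.5, both in HbA1c percentage points; significance level 0.05 (taken as two-sided); power 0.8; attrition 20%.

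**The plan's own figures.** The sensitivity section states no number, so the sample size is the only figure to reproduce. Normal approximation: 2 × (1.960 + 0.8416)² × 1.3² / 0.5² = 2 × 7.849 × 1.69 / 0.25 = 106.1, so 107 per group. The noncentral t calculation gives 108 (power 0.803), as stated. Then 216 / 0.8 = 270 and 270 / 0.9 = 300, also as stated.

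**Step 1: the two conditions side by side.** Let Y0, Y6 and Y12 be HbA1c at the three visits, and let R = 1 if Y12 is missing.

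- As worded: E(Y12 | R = 1) − E(Y12 | R = 0) = 0.
- In the primary model: E(Y12 | arm, clinic, Y0, Y6, R = 1) − E(Y12 | arm, clinic, Y0, Y6, R = 0) = 0.

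The second does not imply the first unless dropout is unrelated to the observed predictors of Y12.

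**Step 2: how far apart they can be.** Three visits were simulated with SD 1.3 and equal correlation between visits. About 20% of values were missing at 12 months, depending only on the observed 6-month value, so missing at random holds by construction. The correlations and the odds ratios for dropout per SD of 6-month HbA1c are assumptions; the document gives none. Regression on baseline and 6-month HbA1c stood in for the mixed model, without clinic effects.

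| Correlation | δ as worded, OR 1.5 | OR 2 | OR 3 |
|---|---|---|---|
| 0.3 | 0.16 | 0.25 | 0.36 |
| 0.5 | 0.26 | 0.42 | 0.60 |
| 0.7 | 0.36 | 0.58 | 0.85 |

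The conditional δ stayed within 0.006 of zero in all nine cases.

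**Step 3: what δ = 0 returns.** If δ as worded is applied within each arm, the arm mean is (observed mean) + p·δ, where p is the proportion missing. At δ = 0 this is the completers' mean. The missing-at-random arm mean is (observed mean) + p·D, where D is the unconditional gap from Step 2. So the completers' difference minus the missing-at-random difference is −(p_I·D_I − p_C·D_C). With a true effect of 0 and p = 0.2 in both arms:

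- OR 2 in intervention, 1 in control, correlation 0.5: −0.2 × 0.418 = −0.084 (simulated completers' difference −0.085).
- Same odds ratios, correlation 0.7: −0.2 × 0.584 = −0.117 (simulated −0.119).
- OR 2 and 0.5, correlation 0.7: −0.2 × (0.584 + 0.584) = −0.234 (simulated −0.233).
- OR 2 in both arms, correlation 0.5: 0 (simulated −0.002).

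The missing-at-random estimate was within 0.002 of zero in all four. The contrast is therefore mis-anchored only when dropout relates to earlier HbA1c differently in the two arms.

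**Step 4: common against arm-specific δ.** With δ defined as an offset from the missing-at-random prediction, effect(δ) = effect(primary) + δ_I·p_I − δ_C·p_C. The δ values and the unequal missing rates are illustrative.

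| Missing, I / C | δ | Common to both arms | Intervention only | Opposite signs |
|---|---|---|---|---|
| 20% / 20% | 0.5 | 0.00 | 0.10 | 0.20 |
| 20% / 20% | 1.0 | 0.00 | 0.20 | 0.40 |
| 22% / 18% | 1.0 | 0.04 | 0.22 | 0.40 |
| 25% / 15% | 0.5 | 0.05 | 0.125 | 0.20 |
| 25% / 15% | 1.0 | 0.10 | 0.25 | 0.40 |

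**Step 5: effect on a conclusion.** With 108 observed per arm the unadjusted standard error is 1.3 × √(2/108) = 0.177, held fixed here. For an estimated effect of −0.40 and 20% missing per arm, the upper 95% limit is −0.40 + 1.96 × 0.177 = −0.05 at every common δ. With δ = 0.5 in the intervention arm only, the estimate is −0.30 and the upper limit is +0.05.

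**The case against.** The best defence is that the sentence is loose rather than wrong in intent. The word unconditional does not appear, and the analysis is placed within the primary mixed model, with δ meant to express departure from that model's assumption. A competent analyst might well implement δ as an offset from the model's prediction. That is possible, but the wording does not say it, and the explanation of the sign of δ repeats the comparison of participants with missing data against observed participants. A condensed article may leave out a grid of values; brevity does not account for a condition that is stated incorrectly.

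Three stronger readings are tempting and are not supported:

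- A reader might infer that the plan applies one common δ to both arms and will therefore report false robustness. The document never says so. It uses one symbol without an arm index and is silent on the rest. Even with a common δ, the shift is zero only if missingness is equal in the arms; at 25% against 15% it is 0.05 for δ = 0.5.
- A reader might infer that differences between arms will be ignored. The section does plan to compare drop-out by arm, and arm-specific δ is neither adopted nor excluded.
- A reader might infer that mis-anchoring necessarily biases the treatment contrast. Step 3 shows the gap vanishing when dropout works alike in both arms.

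The Discussion's caveat that the mixed model satisfies intention to treat "provided the missing at random assumption holds" is correct and is not part of the error.

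**Conclusion.** The statement that δ, as defined, is zero under missing at random is wrong for the model the plan specifies, and should be corrected. Under assumed correlations of 0.3 to 0.7 and dropout odds ratios of 1.5 to 3 per SD, with 20% missing, the stated δ is 0.16 to 0.85 HbA1c percentage points when missing at random holds exactly. Taken literally within each arm, δ = 0 gives a completers' comparison. Its distance from the primary estimate was 0.09 to 0.23 in the simulated cases where dropout depended on 6-month HbA1c differently by arm, and nil where it did not.

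The point about arms is conditional. The text makes no provision for δ to differ by arm. If a common δ were used with similar missingness, the check would be uninformative: 0.00 at 20% / 20%, against 0.20 (0.20 / 0.5 = 40% of the target difference) for δ = 1.0 in one arm only. Whether that would happen cannot be told from the article. The primary analysis and the sample size are unaffected.

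**What to change.** Reword the Sensitivity analysis section so that δ is the mean offset between the unobserved 12-month HbA1c values and those predicted by the primary missing-at-random model from arm, clinic and the participant's observed HbA1c. State that δ = 0 reproduces the primary estimate (up to simulation error if multiple imputation is used).

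Allow separate values δ_I and δ_C. Prespecify a numerical range, with scenarios in which δ applies to the intervention arm only, to the control arm only, and to both. A particular grid, for example −1.0 to +1.0 HbA1c percentage points, and a tipping-point report are useful but optional.

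The cost is a few sentences in the SAP and a few more model runs. No new data are needed.

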## Discussion

The design effect is a multiplier applied to sample size calculations for an individually randomised trial to account for the sampling method, such as stratified or cluster randomisation. In this study, participants will be randomly allocated to study groups stratified by the clinic they attend. For stratified randomised trials the design effect is (1 – ICC), where the intraclass correlation coefficient (ICC) quantifies the correlation of outcomes within clinics. Applying this design effect to the sample size calculations will reduce the number of individuals required for the same power as an individually randomised controlled trial with no stratification when the ICC is greater than zero [31]. For this study, we chose the more conservative sample size that did not adjust for stratification by clinic, that is the ICC was assumed to be zero to avoid challenges associated with estimating the ICC.

Randomly permuted block sizes of 4 and 6 were chosen to minimise differences in the number of participants in each study group should recruitment stop abruptly in a clinic and to ensure adequate participants in each study group for estimation of clinic effects. Random effects were chosen to model the clinic effects as we assumed clinics involved were a random sample across Victoria. Furthermore, random-effects models can perform better than fixed-effects models in terms of power and efficiency when there are a small number of participants per clinic and there are treatment assignment imbalances within clinics [32]. Lastly, the mixed-effects model includes all data observed on the subjects and satisfies the intention-to-treat principle in the presence of missing outcome data, provided the missing at random assumption holds.

This analysis plan was written prior to completion of the trial data collection phase. Analyses are pre-specified, consistent with the study objectives, and not driven by the data. An outcomes paper based on this analysis plan will be available upon completion of data collection, which is anticipated in late 2018.

## Abbreviations

API: Application programming interface
CACE: Complier average causal effect
CAV: Clinic assessment visit
CDE: Credentialed diabetes educator
CGM: Continuous glucose monitoring
CVD: Cardiovascular disease
eGFR: Estimated glomerular filtration rate
EQ-5D-3 L: EuroQol 5 dimension 3 levels
GP: General practitioner
GP-OSMOTIC: General Practice Optimising Structured Monitoring to Improve Clinical Outcomes in Type 2 Diabetes
GUI: Graphical user interface
GV: Glycaemic variability
HbA1c: Glycated haemoglobin
ICC: Intraclass correlation coefficient
ICER: Incremental cost-effectiveness ratio
IRSD: Index of relative socio-economic disadvantage
ITT: Intention-to-treat
PAID: Problem Areas in Diabetes
PBS: Pharmaceutical benefit schedule
PN: Practice nurse
PP: Per-protocol analysis
QALY: Quality-adjusted life year
r-CGM: Retrospective continuous glucose monitoring
REDCap: Research electronic data capture
RN-CDE: Registered nurse credentialed diabetes educator
SD: Standard deviation
T2D: Type 2 diabetes
VAED: Victorian admitted episodes dataset
VEMD: Victorian emergency minimum dataset
